### Intervention description {11a}

This is an observational study. No clinical interventions are administered. All assessments are non-invasive diagnostics.

### Criteria for discontinuing or modifying allocated interventions {11b}

This is an observational study. No clinical interventions are administered. All assessments are non-invasive diagnostics.

### Strategies to improve adherence to interventions {11c}

This is an observational study. No clinical interventions are administered. All assessments are non-invasive diagnostics.

### Relevant concomitant care permitted or prohibited during the trial {11d}

This is an observational study. No clinical interventions are administered. All assessments are non-invasive diagnostics.

### Provisions for post-trial care {30}

This study involves non-invasive observational assessments and does not include administration of any therapeutic or experimental clinical interventions. As such, the risk of physical or psychological harm to participants is minimal.

However, in accordance with national ethical guidelines and institutional policy:Any child identified during the study as having previously undiagnosed or untreated refractive errors or ocular conditions will be referred to the Department of Ophthalmology at AIIMS Bhopal or a nearby government ophthalmic center for appropriate clinical evaluation and care, free of cost under available public health schemes.No post-trial intervention or follow-up treatment is mandated beyond the scheduled study assessments, as no interventional product or device is being tested.In the unlikely event of harm resulting directly from participation in study procedures (e.g., adverse reaction to cycloplegic drops), immediate medical attention will be provided at AIIMS Bhopal, and the participant will be eligible for care and compensation in accordance with the Ethical Guidelines for Biomedical Research on Human Participants (ICMR, 2017) and the guidelines of the Institutional Ethics Committee (IEC).

### Outcomes {12}

#### Primary outcome

Measurement Variable: Risk of myopia progressionAnalysis Metric: Change in spherical equivalent refraction (SER) and axial length over timeMethod of Aggregation: Mean change from baseline to each 6-month follow-up, stratified by age group, urban/rural location, and baseline refractive statusTime Points: Baseline, 6 months, 12 months, 18 months, and 24 monthsClinical Relevance**:** Monitoring SER and axial elongation is clinically validated as the gold standard for quantifying myopia progression. Accurate prediction supports early intervention and reduces the risk of long-term complications such as retinal detachment and macular degenerationThe AI model performance metrics (e.g., AUROC, sensitivity, specificity) will be evaluated against the primary clinical outcome of myopia progression (change in spherical equivalent refraction and axial length), thereby linking predictive accuracy directly to clinically meaningful disease progression

#### Secondary outcomes

AI Model Performance MetricsoMeasurement Variables: Accuracy, sensitivity, specificity, F1 score, AUROC (Area Under Receiver Operating Characteristic Curve)oAnalysis Metric: Model performance against test dataoMethod of Aggregation: Aggregated over cross-validation folds and independent test setsoTime Point: After complete data collection at each longitudinal stageoClinical Relevance: Demonstrates the utility of AI for triage and risk stratification without immediate clinical interventionIdentification of Dominant Risk FactorsoMeasurement Variables: Screen time, parental myopia, near work duration, outdoor activity, corneal curvature, axial length, etc.oAnalysis Metric: Feature importance scores and multivariate regression coefficientsoMethod of Aggregation: Ranked predictive power in final AI modeloTime Point: End of Phase 1 (cross-sectional analysis)oClinical Relevance: Supports public health planning and targeted interventionsMobile Application Usability and AccuracyoMeasurement Variables: Accuracy of app-based predictions compared to clinical diagnosesoAnalysis Metric: Positive predictive value, user-reported ease-of-use scoresoMethod of Aggregation: Mean values and usability ratings (Likert scale)oTime Point: Pilot deployment at 18 monthsoClinical Relevance: Determines the viability of a scalable school-level screening tool

#### Exploratory outcomes

Awareness and behavior change: Number of students reached and qualitative feedback on myopia prevention education initiativesData Quality Indicators: Completeness and reliability of longitudinal data across follow-up visits

### Participant timeline {13}

Participants will be enrolled and followed up over a 36-month period as per the schedule below:

#### Phase 1: baseline cross-sectional survey (months 1–12)

Enrolment and Consent: Months 1–3Baseline Assessment (Ocular and Demographic): Months 2–9Initial Data Cleaning and Preprocessing: Months 6–12AI Model (v1) Training on Baseline Data: Months 9–12

#### Phase 2: longitudinal follow-up cohort (months 13–36)

Cohort Selection (10% of Phase 1): Month 13Follow-up Assessments:oVisit 1: Month 18oVisit 2: Month 24oVisit 3: Month 30oVisit 4: Month 36AI Model Refinement: Ongoing after each follow-up roundMobile App Pilot Testing: Month 30–36

**Schematic diagram of study timeline**

**Table Tabb:** 

Study period	Enrolment	Baseline (T0)	Follow-up 1 (T1)	T2	T3	T4
Time point (months)	0–3	2–9	18	24	30	36
Informed consent	✔					
Eligibility assessment	✔					
Demographic data		✔				
Ocular examinations		✔	✔	✔	✔	✔
Questionnaire		✔	✔	✔	✔	✔
AI model training		✔	✔	✔	✔	✔
Mobile App testing					✔	✔

### Sample size {14}

The estimated number of participants required to achieve the study’s objectives is 5,000 school-going children for the baseline cross-sectional phase, with a 10% subcohort (approximately 500 children) followed longitudinally over a period of 24 months.

#### Phase 1: cross-sectional component

A minimum sample size of 1640 children was initially calculated based on:Expected incidence rate of myopia: 3.4% (as per Saxena et al., 2017; PLoS ONE, North India Myopia Study)Confidence level: 95% (*Z* = 1.96)Precision (d): 2.5%

Sample size formula used:

N = Z2 × p × (1 − p)d2N = \frac{Z^2 \times p \times (1—p)}{d^2}N = d2Z2 × p × (1 − p)​ N = (1.96)2 × 0.034 × (1 − 0.034)(0.025)2≈1,484N = \frac{(1.96)^2 \times 0.034 \times (1—0.034)}{(0.025)^2} ≈ 1,484N = (0.025)2(1.96)2 × 0.034 × (1 − 0.034)​≈1,484.

Adjusting for a 10% non-response or attrition rate:

N≈1,640N ≈ 1,640N≈1,640

To increase statistical power and allow for subgroup analysis (by age, gender, urban/rural, socioeconomic status), the sample was scaled up to 5000 participants, ensuring diversity and enabling robust AI model training with stratified data.

#### Phase 2: longitudinal cohort

A subset of 10% (approx. 500 children) will be selected from Phase 1 using AI-based parameter selection and stratified sampling (equal representation of myopic and non-myopic participants). This sample size is adequate for:Detecting meaningful differences in myopia progression rates (in diopters and axial length)Training and validating AI models using longitudinal data with multiple follow-upsEnsuring sufficient statistical power (> 80%) for machine learning model performance metrics such as AUC, sensitivity, and specificity

Sample size assumptions were determined in consultation with biostatisticians and are justified based on the objectives of developing and validating a predictive AI tool, rather than testing clinical efficacy of an intervention.

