## Assignment of interventions: allocation

### Sequence generation {16a}

This study does not involve random allocation to intervention or control groups, as it is a non-interventional observational cohort trial.

However, for the purpose of selecting a representative 10% sub-cohort (approximately 500 children) from the cross-sectional sample for longitudinal follow-up, a structured sampling process will be used:The allocation sequence for follow-up selection will be generated using a computerized stratified random sampling algorithm.Stratification factors will include:oBaseline myopia status (myopic vs. non-myopic)oAge group (6–10, 11–14, 15–18 years)oGeographic location (urban vs. rural)oGender

This approach will ensure balanced representation across key demographic and clinical subgroups, thereby enhancing the generalizability of AI model training and validation.

The specific algorithm and code for allocation will be maintained by the data analysis team at MANIT Bhopal and will not be accessible to field teams or investigators responsible for participant enrolment to avoid selection bias.

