### Concealment mechanism {16b}

As this is a non-randomized, observational cohort study, there is no allocation to therapeutic or intervention groups. Therefore, conventional allocation concealment (e.g., sealed envelopes or centralized randomization) is not applicable.

For the selection of the 10% longitudinal follow-up cohort, a stratified random sampling algorithm will be used, based on pre-specified criteria (myopia status, age group, gender, and geographic area). This sampling will be conducted centrally by the data analysis team at Maulana Azad National Institute of Technology (MANIT), Bhopal, using a computer-generated randomization process.

To minimize selection bias:The allocation sequence will be stored securely and will **not be accessible** to the field teams involved in school visits or data collection.The list of selected participants will be released **only after completion of baseline data collection**, ensuring that the initial assessments are conducted without any influence from the selection status.

This mechanism maintains methodological rigor and reduces the risk of conscious or unconscious selection bias in follow-up participant identification.

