#### Adjusted analyses

Multivariable regression models (e.g., linear or logistic regression for continuous or categorical outcomes, respectively) will be adjusted for potential confounders including:AgeGenderScreen timeDuration of outdoor activitySocio-economic statusParental myopia

These adjustments aim to isolate the effect of independent predictors on myopia progression and improve the interpretability and generalizability of AI-based predictions.

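### The Phase 2 selection rule is stated in two conflicting ways, and a cohort fixed at equal myopic and non-myopic numbers is called representative

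*Protocol article*

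**What the plan says.** Protocol article, Sample size {14}: the requirement "is 5,000 school-going children for the baseline cross-sectional phase", "with a 10% subcohort (approximately 500 children) followed longitudinally over a period of 24 months". Under Phase 2: longitudinal cohort, those children "will be selected from Phase 1 using AI-based parameter selection and stratified sampling (equal representation of myopic and non-myopic participants"). The abstract also describes the cohort as balanced on myopia.

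The allocation sections give the rule without any AI step. Under Sequence generation {16a} the selection list is "generated using a computerized stratified random sampling algorithm", stratified by baseline myopia status, age group (three bands), urban or rural location, and gender. Concealment mechanism {16b} says that "a stratified random sampling algorithm will be used, based on pre-specified criteria (myopia status, age group, gender, and geographic area"). Implementation {16c} repeats this.

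Sequence generation {16a} gives the purpose as "selecting a representative 10% sub-cohort (approximately 500 children") and says the balance improves the generalizability of model training and validation.

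In Participant timeline {13}, model v1 is trained on baseline data in Months 9–12 and the cohort is selected in Month 13. Accuracy, sensitivity, specificity, F1 and AUROC are listed under Outcomes {12}, and AUPRC is added in Statistical methods {20a}. Neither section mentions sampling weights or recalibration.

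**The concern.** Two separate problems meet in the same step.

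First, the two descriptions are different designs. A random draw within fixed strata gives every child a known chance of selection, so results can be carried back to the 5,000. A draw steered by model output, or by predictors that a model has picked, does not. Inclusion would then depend on the variables the study means to rank and validate, with no probability attached. The timeline makes this reading possible, because a trained model will exist one month before selection. Once children have been chosen under an undocumented rule, later weighting cannot repair the cohort.

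Second, oversampling myopic children is a legitimate way to gain progression events, but it is the opposite of overall representativeness. Pooled F1, AUPRC and AUROC, calibration where it is assessed, and any PPV computed in this cohort depend on case mix. The model is meant for a school-level screening app, where the case mix will differ.

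**Working it through.** **Cohort size.** 10% × 5,000 = 500, and 500/2 = 250 per myopia group. This reproduces the plan's figure.

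**Selection rules side by side.** Sample size {14} has AI-based parameter selection plus stratification. Sections {16a} to {16c} have stratified random sampling on four named factors and no AI step; {16b} calls the criteria pre-specified. A model-driven element and criteria fixed in advance cannot both be the whole rule.

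**Representativeness.** The document gives no baseline prevalence p of myopia, so p is an assumption here. For a 250:250 sample the fractions are 250/(5,000p) for myopic and 250/(5,000(1−p)) for non-myopic children. The design weights are p/0.5 and (1−p)/0.5, and the Kish effective size is 500/(0.5·w₁² + 0.5·w₂²).

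| Assumed p | Fraction, myopic | Fraction, non-myopic | Ratio | Weights | Effective n |
|---|---|---|---|---|---|
| 5% | 100% | 5.3% | 19 | 0.10 / 1.90 | 276 |
| 10% | 50% | 5.6% | 9 | 0.20 / 1.80 | 305 |
| 20% | 25% | 6.3% | 4 | 0.40 / 1.60 | 368 |
| 30% | 16.7% | 7.1% | 2.3 | 0.60 / 1.40 | 431 |

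The ratio is 1 only at p = 50%. The table counts the myopia split alone. If age, location and gender are also equalised, which the text does not settle, the effective n would change.

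**Effect on pooled metrics.** Assumptions, none from the document: 40% of myopic and 5% or 10% of non-myopic children progress, and sensitivity = specificity = 0.80 throughout.

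- Event rate in the cohort: 0.5×0.40 + 0.5×0.05 = 0.225, or 0.25 with 10%.
- Event rate at p = 10%: 0.1×0.40 + 0.9×0.05 = 0.085, or 0.13 with 10%.
- PPV = 0.8π/(0.8π + 0.2(1−π)), where π is the event rate.
- Cohort PPV: 0.180/0.335 = 54%, or 0.200/0.350 = 57%.
- PPV at p = 10%: 0.068/0.251 = 27%, or 0.104/0.278 = 37%.
- F1 = 2×PPV×0.8/(PPV + 0.8): 0.64 to 0.67 in the cohort, against 0.40 to 0.51 at p = 10%.
- PPV at other prevalences: 22–34% at p = 5%, 35–43% at 20%, 42–48% at 30%.
- AUROC of baseline myopia status alone, with 40% and 5%: 0.5×(1 + 0.889 − 0.387) = 0.75 in the cohort, and 0.5×(1 + 0.471 − 0.066) = 0.70 at p = 10%.
- Accuracy is 0.80 in every case.

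**Feasibility.** 250/5,000 = 5.0% is the lowest prevalence that yields 250 myopic children, and only if all of them join. The one rate in the sample size section is 3.4%, called an incidence but used as the proportion in the formula. Read as a prevalence, it gives 5,000 × 0.034 = 170, at most 34% of 500.

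**The case against.** **The AI phrase may be loose wording.** Parameter selection could mean choosing the stratification variables, and no section says the v1 model picks children. That is fair, and on this reading the harm is smaller. The conflict remains, because model-chosen strata would not be the four factors listed as pre-specified.

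**A reader might infer that the cohort will be analysed unweighted.** The protocol does not say so. A separate SAP exists and is not shown, and weights could properly be placed there. All that can be said is that the protocol describes none.

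**A reader might infer that the sampling strata are left out of the models.** The text does not support this. The Adjusted analyses section has models "adjusted for potential confounders including:AgeGenderScreen timeDuration of outdoor activitySocio-economic statusParental myopia", which is an open list. The primary mean change is stratified by age group, location and baseline refractive status. Subgroup analyses {20b} plan stratified modelling and interaction terms by location and baseline myopia, and cover model performance by myopia status.

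**A reader might infer that every metric will look better in the cohort.** Accuracy need not. It does not move under the assumptions above, and a rule that always predicts no progression scores 77.5% in the cohort (1 − 0.225) but 91.5% at 10% prevalence (1 − 0.085).

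**The planned PPV belongs to the app pilot.** Its population is not stated, so the PPV figures apply only to a PPV computed in this cohort. The composition of the independent test sets is also not given. The progression risks are assumed, so the sizes illustrate and do not predict.

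**3.4% is labelled an incidence.** If it is one, the 170 does not follow, but the document then gives no prevalence that supports 250.

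**Conclusion.** Two points stand on the text alone. The selection rule is stated in two incompatible ways, and the claims of representativeness and generalizability are wrong for the overall school population unless about half the children are myopic. The first must be settled before the Month 13 draw, because inclusion probabilities that were never defined cannot be recovered afterwards.

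The consequence for pooled prevalence-dependent metrics is real in kind, but its size rests on assumed inputs: under those above, cohort PPV is roughly 1.5 to 2 times its value at 10% myopia prevalence (57/37 and 54/27). It applies where such metrics are computed in this cohort without weighting, which the protocol neither states nor excludes. The feasibility point is conditional: 170 against 250 if 3.4% is a prevalence, and otherwise unsupported either way.

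**What to change.** 1. In Sample size {14}, remove the AI-based parameter selection, so that children are chosen only by random draw within the strata of Sequence generation {16a}.
2. Record the sampling fraction of every stratum (2 × 3 × 2 × 2 = 24 cells) when the list is drawn.
3. Report pooled performance metrics weighted by the inverse of those fractions, beside the results by baseline myopia status already planned.
4. Describe the cohort as stratified and enriched for myopia, and limit the generalizability claim to within-stratum or weighted results.
5. State the shortfall rule: if fewer than 250 myopic children are found, all are taken, the remaining places are filled from the non-myopic strata, and the fractions are recorded.

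The cost is an amendment to the text and one weight column. Weighting widens intervals: the effective size is about 305 of 500 at an assumed 10% prevalence and 276 at 5%. Stratum-specific results do not carry the loss from the myopia split, which is a further reason to show both.

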#### Recruitment {15}

To ensure achievement of the target sample size of 5000 school-going children across urban and rural areas of the Bhopal division, the following strategies will be employed:

Institutional Collaboration:Formal letters of collaboration and administrative approvals have been obtained from district education authorities and individual schools to facilitate access to eligible students across five districts (Bhopal, Raisen, Rajgarh, Sehore, and Vidisha).School-based outreach:Recruitment will be conducted through government and private schools identified via stratified sampling. Each school will be visited by the study team to conduct parent–teacher meetings, distribute participant information sheets, and explain the study process in local languages.Awareness and engagement sessions:Educational sessions and eye health awareness activities will be conducted in schools to enhance participation. These sessions will inform parents and students about the importance of early myopia detection and the non-invasive nature of the assessments.Dedicated field teams:Multiple trained field teams (ophthalmologists, optometrists, and research assistants) will be deployed simultaneously across districts to maximize enrolment efficiency and geographic coverage.Flexible scheduling:Data collection visits will be coordinated with school administrators to minimize disruption to academic schedules and maximize attendance during assessment days.Follow-up cohort retention:For the longitudinal phase, participants selected for follow-up will be enrolled with parental consent for periodic re-assessments every six months, with SMS/phone reminders and on-site visits planned to maintain cohort continuity.

These recruitment strategies are designed to ensure representative sampling, minimize attrition, and achieve timely enrolment within the project timeline.

## Assignment of interventions: allocation

### Sequence generation {16a}

This study does not involve random allocation to intervention or control groups, as it is a non-interventional observational cohort trial.

However, for the purpose of selecting a representative 10% sub-cohort (approximately 500 children) from the cross-sectional sample for longitudinal follow-up, a structured sampling process will be used:The allocation sequence for follow-up selection will be generated using a computerized stratified random sampling algorithm.Stratification factors will include:oBaseline myopia status (myopic vs. non-myopic)oAge group (6–10, 11–14, 15–18 years)oGeographic location (urban vs. rural)oGender

This approach will ensure balanced representation across key demographic and clinical subgroups, thereby enhancing the generalizability of AI model training and validation.

The specific algorithm and code for allocation will be maintained by the data analysis team at MANIT Bhopal and will not be accessible to field teams or investigators responsible for participant enrolment to avoid selection bias.

### Concealment mechanism {16b}

As this is a non-randomized, observational cohort study, there is no allocation to therapeutic or intervention groups. Therefore, conventional allocation concealment (e.g., sealed envelopes or centralized randomization) is not applicable.

For the selection of the 10% longitudinal follow-up cohort, a stratified random sampling algorithm will be used, based on pre-specified criteria (myopia status, age group, gender, and geographic area). This sampling will be conducted centrally by the data analysis team at Maulana Azad National Institute of Technology (MANIT), Bhopal, using a computer-generated randomization process.

To minimize selection bias:The allocation sequence will be stored securely and will **not be accessible** to the field teams involved in school visits or data collection.The list of selected participants will be released **only after completion of baseline data collection**, ensuring that the initial assessments are conducted without any influence from the selection status.

This mechanism maintains methodological rigor and reduces the risk of conscious or unconscious selection bias in follow-up participant identification.

### Implementation {16c}

As this is an observational study without intervention groups, participants are not assigned to interventions. However, a selection process is used to identify a 10% sub-cohort from the baseline sample for longitudinal follow-up. The roles related to this process are as follows:Generation of the Allocation Sequence:The stratified random sampling algorithm used to select participants for follow-up will be developed and executed by the data science team at Maulana Azad National Institute of Technology (MANIT), Bhopal). The algorithm will be based on predefined strata (e.g., myopia status, age group, gender, and geographic region).Enrollment of Participants:Participants will be enrolled at the school level by trained ophthalmologists and research staff from AIIMS Bhopal, following informed consent from parents or legal guardians and assent from children (as applicable).Assignment to Longitudinal Follow-Up:The list of selected participants for the follow-up phase will be generated only after completion of baseline assessments, and those participants will be contacted by the field team from AIIMS Bhopal for scheduling periodic reassessments. The enrolment team will have no influence over the selection process.

This separation of roles ensures objectivity, prevents selection bias, and preserves the integrity of cohort formation.

